# 1 Administrative information

This document was constructed using the Comprehensive Clinical Trials Unit (CCTU) at UCL Protocol template Version 4. It describes the FACT trial, sponsored by UCL and co-ordinated by CCTU.

It provides information about procedures for entering participants into the trial, and provides sufficient detail to enable: an understanding of the background, rationale, objectives, trial population, intervention, methods, statistical analyses, ethical considerations, dissemination plans and administration of the trial; replication of key aspects of trial methods and conduct; and appraisal of the trial’s scientific and ethical rigour from the time of ethics approval through to dissemination of the results. The protocol should not be used as an aide-memoire or guide for the treatment of other patients. Every care has been taken in drafting this protocol, but corrections or amendments may be necessary. These will be circulated to registered investigators in the trial. Sites entering participants for the first time should confirm they have the correct version by contacting the FACT Trial Manager at CCTU.

CCTU supports the commitment that its trials adhere to the SPIRIT guidelines. As such, the protocol template is based on an adaptation of the Medical Research Council CTU protocol template (2012) and the Standard Protocol Items: Recommendations for Interventional Trials (SPIRIT) 2012 Statement for protocols of clinical trials (32). The SPIRIT Statement Explanation and Elaboration document (33) can be referred to, or a member of CCTU Protocol Review Committee can be contacted for further detail about specific items.

## 1.1 Compliance

The trial will be conducted in compliance with the approved protocol, the Declaration of Helsinki (2008), the principles of Good Clinical Practice (GCP) as laid down by the Commission Directive 2005/28/EC with implementation in national legislation in the UK by Statutory Instrument 2004/1031 and subsequent amendments, the UK Data Protection Act, and the National Health Service (NHS) Research Governance Framework for Health and Social Care (RGF). Agreements that include detailed roles and responsibilities will be in place between participating sites and CCTU.

Participating sites will inform CCTU as soon as they are aware of a possible serious breach of compliance, so that CCTU staff can fulfil requirements to report the breach if necessary to the CCTU Quality Management Group (QMG). A ‘serious breach’ is one that is likely to affect to a significant degree:

- The safety or physical or mental integrity of the subjects in the trial, or
- The scientific value of the trial.

## 1.2 Sponsor

UCL is the trial sponsor and has delegated responsibility for the overall management of the FACT trial to CCTU. Queries relating to UCL sponsorship of this trial should be addressed to the CCTU Director or via the trial team.

## 1.3 Structured trial summary

| Primary Registry and Trial Identifying Number | ISRCTN77602616 |
| --- | --- |
| Date of Registration in Primary Registry | 6^th^ January 2015 |
| Secondary Identifying Numbers |  |
| Source of Monetary or Material Support | National Institute of Health Research (HTA) |
| Sponsor | University College London with sponsor responsibilities delegated to CCTU. |
| Contact for Public Queries | FACT Trial Manager  UCL Comprehensive Clinical Trials Unit  [name]  [name]  [contact] |
| Contact for Scientific Queries | [name]  Consultant Ophthalmologist  Moorfields Eye Hospital NHS Foundation Trust  [name]  [name]  [[contact]](mailto:[contact])  [name] |
| Public Title | FACT: Laser assisted versus standard ultrasound cataract surgery |
| Scientific Title | The FACT trial: A randomised, single masked, non-inferiority trial of **F**emtosecond laser **A**ssisted vs. manual phacoemulsification **C**a**T**aract surgery for adults with visually significant cataract |
| Countries of Recruitment | United Kingdom |
| Health Condition(s) or Problem(s) Studied | Patients with visually symptomatic cataract(s) |
| Intervention(s) | Arm A: Manual Phacoemulsification cataract surgery in the study eye  Arm B: Laser Assisted Phacoemulsification cataract surgery in the study eye  **NB. The study eye is defined as the first eye to undergo cataract surgery that is chosen by the patient in discussion with the surgeon. The allocated intervention will be used for patients having surgery on both eyes unless the patient expresses a wish not to receive the same intervention.** |
| Key Inclusion and Exclusion Criteria | *Inclusion criteria*   - Adults aged 18 or over with visually symptomatic cataract, one or both eyes. - Patients must be sufficiently fluent in English to provide informed consent and completion of the patient reported outcome measures. - Patients must be willing to attend for follow up at 3 and 12 months following surgery to the study eye. - Post-operative intended refractive target in the study eye is within ±0.5 dioptres emmetropia.  *Exclusion criteria*   - Eyes with corneal ring and/or inlay implant(s), or severe corneal opacities, corneal abnormalities, significant corneal oedema or diminished aqueous clarity that is likely to obscure OCT imaging of the anterior lens capsule - Descemetocele with impending corneal rupture - Poor pupil dilation that is expected to require surgical iris manipulation - Subluxed crystalline lens. - Patient unable to give consent or unable to attend follow-up assessment. - Patient unable to be positioned for surgery. - Patient scheduled to undergo combined surgery e.g. cataract and trabeculectomy. - Any contraindications to cataract surgery. - Any clinical condition which the investigator considers would make the patient unsuitable for the trial, including pregnancy.   These inclusion and exclusion criteria have been kept to a minimum to ensure the trial is representative of clinical practice. Pre-existing ocular comorbidity such as age related macular degeneration, diabetic retinopathy or glaucoma will not be reasons for exclusion.  If a participant is currently taking part in another clinical trial it will be at the discretion of the Chief Investigator to decide whether they may also be recruited to the FACT trial. Cases should be assessed on an individual basis. |
| Study Type | The trial is a pragmatic, randomised single masked non-inferiority trial to determine if the proposed advantages of laser assisted cataract surgery translates to real benefits for both patients and the NHS. |
| Date of First Enrolment | By 1^st^ May 2015 |
| Target Sample Size | 808 |
| Primary Outcome(s) | Unaided distance visual acuity (UDVA, logMAR) at 3 months following surgery on the study eye, measured using a standard ETDRS chart at a starting distance of 4 metres. |
| Key Secondary Outcomes | 1. Unaided distance visual acuity (UDVA) at 12 months following surgery in the study eye. 2. Corrected distance visual acuity (logMAR) at 3 and 12 months following surgery in the study eye (ETDRS logMAR chart at a starting distance 4 metres). 3. Ocular complications within 3 and 12 months of surgery in the study eye. A complication will be defined as any event that causes unintentional injury to an ocular structure, or requires additional treatment, or has a negative effect on a patient's health or eyesight. 4. Unaided and corrected visual acuity (using the ETDRS chart at a starting distance of 4 metres) and complications in the second eye (for those with bilateral cataracts), and with both eyes open at 3 and 12 months following surgery on the study eye 5. Proportion of patients with vision within 0.5 and within 1 dioptre of the intended refractive outcome at 3 and 12 months following surgery on the study eye. 6. Patient reported outcome: vision health status at 3, 6 and 12 months: Catquest-9SF (26) 7. Cost-utility analysis: Within-trial cost-effectiveness analyses at 12 months and expected cost- effectiveness over patient lifetime. 8. Corneal endothelial cell count (additional safety measure) in both eyes at 3 and 12 months following surgery in the study eye. |

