## 5.6 Participant Timeline

**Figure 1: Schedule of Assessments**

|  | Standard pre-assessment (for study and non-study patients) | **Baseline** | **Randomisation** | **Follow up** | | | | |
| --- | --- | --- | --- | --- | --- | --- | --- | --- |
|  |  | Surgical Pre Assessment Visit | Randomisation and surgery | Standard non-study post-op appt | 6 weeks post-surgery (by post)  (ideally +/-14 days) | 1^st^ trial apt: 3 months post-surgery  (ideally +/-14  days) | 6 months post-surgery  (by post)  (ideally+/-14  days) | 2^nd^ trial apt: 12 months post-surgery  (ideally +/-14 days) |
| Visit Number | *1* | *1 or later* | 2 | *3* |  | *4* |  | *5* |
| Past medical and ocular history | X | X |  |  |  |  |  |  |
| Consent for cataract surgery | X |  |  |  |  |  |  |  |
| Informed Consent & eligibility screening |  | X |  |  |  |  |  |  |
| Identification of study eye |  | X |  |  |  |  |  |  |
| Visual acuity: UDVA, pinhole, +/- glasses (Snellen), each eye | X |  |  | X |  |  |  |  |
| Visual Acuity: UDVA^1^ & CDVA^2^ (logMAR) each eye and binocular |  |  |  |  |  | X |  | X |
| Visual acuity (LogMAR) with usual method of correction |  |  | X^7^ |  |  |  |  |  |
| Subjective refraction |  |  |  |  |  | X |  | X |
| Ocular biometry | X |  |  |  |  |  |  |  |
| Pentacam corneal topography | X^6^ | X |  |  |  | X |  | X |
| Optical coherence tomography (OCT)^3^ | X^6^ | X^8^ |  | X^6^ |  | X |  | X |
| Inclusion/Exclusion Criteria |  | X |  |  |  |  |  |  |
| Catquest-9SF questionnaire |  | X |  |  | X | X | X | X |
| EQ-5D-3L+vision bolt-on question (EQ-5DV) |  | X |  |  | X | X | X | X |
| CSRI^5^ |  | X |  |  |  | X | X | X |
| Endothelial cell count measurement | X^6^ | X^8^ |  |  |  | X |  | X |
| Surgery |  |  | X |  |  |  |  |  |
| Adverse Event Collection |  |  |  |  | X | X | X^4^ | X |

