## 5.9 Assignment of Intervention

### 5.9.1 Allocation

#### 5.9.1.1 Sequence generation

Patients will be randomised in a 1:1 ratio to either surgical procedure via the Sealed Envelope.com website. Sealed Envelope is a randomisation service provider that provides a proven, reliable and centralised randomisation system. The system will be custom designed to the trial requirements.

This will use minimisation with a random element with stratification by a) treatment centre, b) surgeon, and c) whether in the local clinician’s opinion, the patient will require surgery on one or both eyes.

A random trial arm allocation will be computer generated. Sealed Envelope will provide the randomised treatment for each participant.

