#### 5.10.4.2 Statistical Methods – Outcomes

The primary outcome is uncorrected distance visual acuity at 3 months following surgery on the study eye, measured using an ETDRS chart at a starting distance of 4 metres. Mean UDVA will be reported together with a two-sided 95% confidence interval. This will be compared between treatment groups using regression analysis adjusting for baseline habitual logMar^[[1]](#footnote-2)^ visual acuity and the randomisation stratifiers (treatment centre, surgeon, and whether or not patients have one or both eyes eligible). We will include trial site in our regression models as a fixed effect and surgeon as a random effect. If the upper end of the 95% CI for the difference between means does not cross the non-inferiority limit of 0.1 logMAR, then laser surgery will be regarded as non-inferior. If the mean difference is negative and its 95% CI lies wholly to the left of zero, then we can conclude that laser surgery is superior to manual surgery. We will perform sequential testing of the non-inferiority and superiority hypotheses.

Secondary continuous outcomes such as uncorrected distance visual acuity at 12 months, corrected distance visual acuity and patient reported outcome measures Catquest-9SF will be analysed in a similar fashion. The percentage of study eyes experiencing adverse events (e.g. posterior capsule tears, dropped lens) in the two groups will be compared using Fisher’s exact tests.

In addition regression analyses will be performed for continuous outcomes such as corrected distance visual acuity at 12 months for the study eye, adjusting for baseline habitual logMar visual acuity and the randomisation stratifiers (treatment centre, surgeon, and whether or not patients have one or both eyes eligible). Baseline habitual logMar visual acuity is only collected for the study eye and therefore distance visual acuity outcomes for the fellow eye, whether they are unaided or corrected, will only be adjusted for the randomisation stratifiers.

Pearson’s correlation coefficients (or Spearman’s rank correlation coefficients, depending on the distribution of the data) will be used to assess the relationships between the continuous objective and subjective outcome measures.

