#### 5.10.4.3 Additional Analyses - Subgroup

Planned subgroup analyses will be conducted to investigate possible interactions between treatment effects and whether or not surgery was required on both eyes, with separate estimates and confidence intervals being reported for such patients. We will also investigate a possible interaction between treatment effect and trial site as a pre-specified subgroup analysis.

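### Ocular comorbidity is admitted by design and recorded before surgery, but is not among the acuity models' named covariates, so the trial forgoes a modest gain in precision

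*Protocol*

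**What the plan says.** **Eligibility.** The structured trial summary (protocol 1.3) admits diseased eyes on purpose: "Pre-existing ocular comorbidity such as age related macular degeneration, diabetic retinopathy or glaucoma will not be reasons for exclusion". The reason given is generalisability: "These inclusion and exclusion criteria have been kept to a minimum to ensure the trial is representative of clinical practice".

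**Allocation.** Section 5.9.1.1 uses minimisation with "stratification by a) treatment centre, b) surgeon" and the expected need for surgery on one or both eyes.

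**Primary model.** Section 5.10.4.2 specifies "regression analysis adjusting for baseline habitual" logMAR acuity. It adds "the randomisation stratifiers (treatment centre, surgeon, and whether or not patients have one or both eyes eligible). We will include trial site" as a fixed effect, with surgeon as a random effect. Other continuous outcomes are to be handled similarly. Fellow-eye acuity is adjusted for the stratifiers only.

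**Subgroups.** Section 5.10.4.3 plans to examine "possible interactions between treatment effects and whether or not surgery was required on both eyes", and interaction with trial site.

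**Data available before surgery.** Figure 1 in section 5.6 schedules "Past medical and ocular history" at pre-assessment and baseline. Its footnotes place OCT in the standard work-up of all patients and define the baseline acuity measure as current glasses or unaided.

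**The concern.** The protocol names its covariates and subgroups, and neither list contains a prognostic factor that the eligibility rule deliberately lets in. Final acuity in an eye with macular disease, diabetic retinopathy or glaucoma may be limited by the retina or optic nerve, whatever the operation achieves.

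Habitual acuity is an incomplete substitute. In an eye with cataract it combines lens opacity and uncorrected refractive error, both of which surgery addresses, with retinal or nerve disease, which surgery does not. Two eyes with the same habitual acuity can therefore have quite different postoperative potential.

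What is at stake is the width of the interval compared with the 0.1 logMAR margin. A baseline variable that predicts the outcome and is already collected would narrow that interval at almost no cost.

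**Working it through.** **Inputs from protocol 5.7:** margin 0.1 logMAR, SD 0.32, true difference 0, two-sided 95% interval, 90% power, mean cluster size 50, ICC 0.012, dropout 15%.

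**1. Reproduce the plan.**
- Per group: n = 2(1.960 + 1.282)² × 0.32² / 0.1² = 215.2, rounded up to 216, so 432 in total. This agrees with the protocol.
- Design effect: 1 + 49 × 0.012 = 1.588. Then 216 × 1.588 = 343.0, rounded up to 344, so 688 in total. This agrees.
- Dropout: 432 × 1.588 = 686.0, and 686/0.85 = 807.1, which gives 808. Starting from 688 gives 809.4, or 810. The difference is trivial.

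No step reduces the SD for any covariate.

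**2. Power as planned, at 688 evaluable.**
- Effective n per group = 344/1.588 = 216.6.
- SE = 0.32 × √(2/216.6) = 0.0307.
- Half-width = 1.96 × 0.0307 = 0.060.
- Power = Φ(0.1/0.0307 − 1.96) = 90.2%.

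**3. With comorbidity in the model.** Let R² be the share of the planning variance that comorbidity explains beyond the planned covariates. The SD becomes 0.32 × √(1 − R²). R² is an assumption; the protocol gives no figure.

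| R² | SD | 95% half-width | Power |
|---|---|---|---|
| 0 | 0.320 | 0.060 | 90.2% |
| 0.05 | 0.312 | 0.059 | 91.6% |
| 0.10 | 0.304 | 0.057 | 92.9% |
| 0.20 | 0.286 | 0.054 | 95.3% |

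**4. Is that range of R² plausible?** For a yes/no factor with prevalence p and mean acuity shift d, the share explained is p(1 − p)d²/0.32². Both p and d are assumed:
- p = 0.10, d = 0.10: 0.0009/0.1024 = 0.9%
- p = 0.30, d = 0.25: 0.0131/0.1024 = 12.8%
- p = 0.40, d = 0.30: 0.0216/0.1024 = 21.1%

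These shares are before any overlap with habitual acuity, so the usable R² is lower by an unknown amount. At the bottom of the range, power is 90.4% and the gain is negligible.

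**5. Chance imbalance.** With p = 0.30, d = 0.25 and 344 per group, imbalance contributes an SE of 0.25 × √(2 × 0.21/344) = 0.009 logMAR, or about ±0.017 at 95%. The planned half-width of 0.060 already contains this variation.

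**The case against.** **This belongs in the SAP.** Section 5.10.4.1 promises a detailed SAP, which is not among the documents at hand and may already add covariates. That stands as a reason to rate the point as minor. It does not remove the point, because section 5.10.4.2 itself lists the covariates of the primary model.

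**The trial is not underpowered.** This stands. A reader might infer that the omission takes power below 90%. That would follow only if 0.32 described eyes free of comorbidity, in which case power would be 84% to 90% for prevalence 10–40% and shifts of 0.1–0.3 logMAR. The protocol takes the SD from a national database and mentions no such restriction.

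**Dilution towards non-inferiority.** A reader might also infer that eyes unable to show a difference would make inferior surgery look acceptable. Suppose comorbid eyes showed no effect at all and laser were worse by exactly 0.1 logMAR in the rest. The chance of declaring non-inferiority would then rise from 2.5% to 5.1%, 9.5%, 16% and 25% at 10%, 20%, 30% and 40% comorbid eyes. Both the prevalence and the complete non-response are assumptions. Refractive error can still alter unaided acuity in these eyes, and the average effect across routine NHS patients is the trial's stated target. The documents do not support treating that average as biased.

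**The result can be checked.** The data are collected before surgery, so an analysis by comorbidity remains possible. Only its pre-specification in the protocol is absent.

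**Minimisation.** Leaving comorbidity out of the allocation scheme is not an error; randomisation balances it on average.

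**Conclusion.** This is a minor improvement at almost no cost, not a flaw in the design. The named covariates omit a prognostic factor that the trial admits on purpose and records before surgery, and habitual acuity covers it only in part.

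The price is forgone precision: roughly 0 to 5 percentage points of power above a planned level that is met in any case, and at most about 0.006 logMAR of half-width. These figures rest on an assumed R² of up to 0.20 beyond the planned covariates. If habitual acuity already carries most of the comorbidity effect, the gain approaches zero.

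The non-inferiority claim should not be made to depend on a second interval in eyes without comorbidity. At the same SD, power in that subset would be 87%, 83%, 78% and 71% if 10%, 20%, 30% and 40% of eyes were comorbid, and there would be no rule for conflicting results.

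**What to change.** In section 5.10.4.2, add study-eye ocular comorbidity (yes/no) as a fixed covariate in the primary UDVA model and in the other study-eye acuity models. Define it in advance and code it from the pre-randomisation ocular history and OCT, by someone masked to allocation. The protocol does not say which structures the OCT images, so the definition should not rely on the scan alone. The covariate should also enter the imputation model of section 5.10.5, so that the two models agree.

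Optionally, add a treatment-by-comorbidity interaction to section 5.10.4.3, labelled supportive and exploratory, and not a condition for claiming non-inferiority.

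Leave eligibility and minimisation unchanged. The cost is a sentence or two of text, one coded variable and the time to code it, with no new visit, test or patient. The change should be settled before the SAP is finalised.

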## 1.4 Roles and responsibilities

These membership lists are correct at the time of writing; please see terms of reference documentation in the TMF for current lists.

### 1.4.2 Role of trial sponsor and funders

| **Name** | **Affiliation** | **Role** |
| --- | --- | --- |
| UCL |  | Trial Sponsor. |
| UCL CCTU | UCL | Specific functions have been delegated to the UCL CCTU by the Sponsor.  A Clinical Project Manager (CPM) at the UCL CCTU will oversee the Trial Manager and other operations staff who will be responsible for the day-to-day management of the trial and for providing support to the site staff. The CCTU staff will be involved in approaching sites, case report form development, database construction, protocol and participant information in collaboration with the Trial Management Group, and site initiation training. Training will be provided on all aspects of the trial, including the informed consent process and any safety reporting as well as aspects of good clinical practice which will be updated regularly. The CCTU staff will be responsible for routine and triggered monitoring visits, with oversight by the CPM, as well as auditing, if necessary, which will be provided by a member of CCTU staff independent of the trial. Feedback will be via a formal reporting process regarding trial progress and site quality. |
| NIHR HTA | NIHR | Trial Funder |

# 2 Summary Trial Flowchart

Non-study (current) patient cataract surgery pathway

Study patient pathway

(additional steps)

First seen in clinic and listed for cataract surgery

First seen in clinic and listed for cataract surgery.

More detailed measurement of your vision, eye and eye health: done same day or later depending on preference.

Standard ultrasound cataract surgery

Standard ultrasound cataract surgery

Routine patient follow-up at 2-4 weeks

Discharged

Listed for cataract surgery to other eye

Normal ultrasound (phacoemulsification) cataract surgery

Routine patient follow-up at 2-4 weeks

Discharged to local Optometrist

Routine patient follow-up at 2-4 weeks

Listed for cataract surgery to other eye

Cataract surgery on other eye: (same method as 1^st^ eye)

Routine patient follow-up at 2-4 weeks

**3 month study appointment**: repeat detailed measurement of vision, eye and eye health.

**12 month study appointment**: repeat detailed measurement of vision, eye and eye health.

6 week postal questionnaire

6 month postal questionnaire

Laser assisted cataract surgery

Discharged to local Optometrist

# 3 Abbreviations

| AE | Adverse Event | PCR | Posterior Capsule Rupture |
| --- | --- | --- | --- |
| AR | Adverse Reaction | PI | Principal Investigator |
| CI | Chief Investigator | QA | Quality Assurance |
| CRF | Case Report Form | QC | Quality Control |
| CCTU | Comprehensive Clinical Trials Unit | R&D | Research and Development |
| CDVA | Corrected Distance Visual Acuity | REC | Research Ethics Committee |
| CSRI | Client Service Receipt Inventory | SAE | Serious Adverse Event |
| EPT | Effective Phacoemulsification Time | SAP | Statistical Analysis Plan |
| ETDRS | Early Treatment Diabetic Retinopathy Study | SD | Standard Deviation |
| EU | European Union | SHO | Senior House Officer |
| FDA | (US) Food and Drug Administration | SPR | Specialist Registrar |
| FWA | Federal Wide Assurance | SSA | Site Specific Approval |
| GCP | Good Clinical Practice | TMF | Trial Master File |
| HTA | Health Technology Assessment | TMG | Trial Management Group |
| ICC | Intraclass correlation Coefficient | TMT | Trial Management Team |
| ICH | International Conference on Harmonisation | ToR | Terms of Reference |
| IDMC | Independent Data Monitoring Committee | UCL | University College London |
| IOL | Intraocular Lens | UDVA | Uncorrected Distance Visual Acuity |
| IRB | Institutional Review Board | VL | Vision Loss |
| ITT | Intention to Treat |  |  |
| LogMAR | Logarithm of the minimum angle of resolution |  |  |
| NHS | National Health Service |  |  |
| NIHR | National Institute for Health Research |  |  |

